## 1.3 Research Aim, Objectives, and Outcomes

The study explores the possible interventions to improve patients’ therapeutic outcomes by medication adherence, structured diet, and exercise education. The research will investigate the impact of multifactorial interventions by pharmacists and clinical dietitian and electrolyte levels optimisation by physicians on the clinical outcomes in Emirati patients with type 2 diabetes.

The primary outcomes are as follows: (1) to evaluate the impact of pharmacist-led MTM on medications adherence, using a new pharmacist intervention protocol (MPIP), (2) to assess the effect of structure diet and exercise counseling with a specialized dietitian on anthropometry readings and carbohydrate as well as daily energy intake levels compared to control group, and (3) to assess the effect of the multi-factorial interventions on diabetic outcomes, including glycated haemoglobin A1c (HbA1c) level, blood pressure, and lipid profile.

The secondary outcomes are: (1) compare the effect of MPIP on regimen-specific medication possession ratio (MPR), and clinical interventions between both groups, (2) evaluate type, duration, and mean metabolic equivalent of task (METs) of physical activity per week during the follow up period between both groups, and (3) analyse serum electrolyte levels, cardiovascular risk factors, and eGFR levels in both group at study exit.

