## 1.4 Hypothesis and Significance of The Research

In this research, we hypothesise that adherence to medication and exercise, in type 2 diabetic patients, will lead to improvement in patients’ clinical outcomes. The interventions in this research will offer recommendations for healthcare providers to adopt reliable measurable factors to improve diabetic outcomes, which eventually will lessen the burden of diabetes, medication cost in UAE and improve patient satisfaction by reducing or delaying macrovascular complications from diabetes.

In this study medication adherence will be measured by a validated Arabic version of medication adherence questionnaire, which is new in our region and in UAE. The revised Summary of Diabetes Self-Care Activities measure (SDSCA) scale will be used to evaluate adherence to diet and exercise was validated numerically. Moreover, the effects of different serum electrolytes levels including serum sodium, potassium, and magnesium levels on kidney function during the diabetes course will be investigated in this research.

The expected outcomes of the research are summarized as follow:

- Improve medication adherence measured by fixed medication possession ratio (MPR) equation and a validated questionnaire with the new pharmacy intervention protocol in the intervention compared to the control group.
- Achieve better exercise and diet adherence with overall reduction in total carbohydrate and energy intake in the intervention compared to the control group.
- Increase the number of patients reaching the target HbA1c level of < 7% and blood pressure target of 130/80 after one year in the intervention compared to the control group.
- Improved serum electrolyte levels (including serum Na, K, and Mg) in the intervention compared to the control group.
- Reduction in cardiovascular risk factors (such as wight and BMI) and improvement in eGFR levels in the intervention compared to the control group, within the study observation period.

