Each participant in the intervention group will receive a 15- to 30-min counselling session at the initial visit and each scheduled follow-up visit which will occur every 3 months. During these sessions, the pharmacist will assess medication adherence with a validated adherence questionnaire (Appendix 3) and counsel the patients on the importance of medication adherence on clinical outcomes. The barriers to medication adherence will be identified, discussed with the patient, and resolved as much as possible. Finally, the patient will be provided with two or three months of medication supply, and the medication refill date will be documented for medication adherence calculation using the medication possession ratio (MPR) [42, 43].

After each visit, each participant in the intervention group will receive a 15-minute follow-up phone interview within two weeks for adherence reinforcement and to address any non-compliance issues or medication side effects. Moreover, they will be scheduled for their next medication refill and follow-up visits in the clinic appointment system. Appointments will be scheduled at months 3, 6, and 12 from the initial visit according to the patient’s preferred date, and they will receive a reminder phone call three days before the next visit from the clinic call centre.

Medication adherence will be evaluated using two techniques during the follow-up period: calculating the medication adherence possession ratio and the medication adherence questionnaire scores.

1. Medication Adherence Possession Formulas

In this study, we will use three formulas to calculate medication adherence from patients’ medication refills recorded in Salamtak:

1. Total Fixed Medication Possession Ratio (MPRt)

A fixed medication possession ratio (MPR) formula will be used to measure total (composite) adherence to all medications (MPRt) [44, 45]. The MPRt will be calculated for three chronic regimens including antihyperglycaemic, antihypertensive and antihyperlipidaemic regimens.

For the total MPRt, no regimen-specific MPR (MPRs) will be measured. It is calculated by summing the days’ supply of medication per prescription, then dividing by the number of days of patient follow-up, using a fixed follow-up period of 365 days (12 months) as a constant denominator, adjusted to hospital stay if the participant was admitted during the follow-up period (Figure 2).

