In addition to the MPR calculation, we will estimate the regimen non-persistence (RNP) or days without medication for each regimen (diabetic, hypertensive, and antihyperlipidaemic regimens) the patient had during the study [48], calculated as the total number of days the patient did not receive one or more medications for any of the patient’s chronic regimen divided by the total follow-up days.

$$\text{RNP}\text{ }\text{=}\frac{\sum\text{Days of supply of medication in a regimen}}{\text{Days of follow-up period}}$$

1. Medication Adherence Questionnaire

A validated medication adherence questionnaire translated into Arabic, showing sufficient reliability with adequate internal consistency, will be used initially to measure medication adherence at baseline for all study participants, and subsequently at each follow-up visit in the intervention group and again at the study exit (Appendix 3)[41].

The questionnaire contains four medication adherence questions from the validated Arabic version of the tool: 1) “Do you ever forget to take your medicine?” and 2) “Are you careless at times about taking your medicine?”, 3) “When you feel better do you sometimes stop taking your medicine??”, 4) “Sometimes if you feel worse when you take the medicine, do you stop taking it?”.

The total score of the medication adherence questionnaire included the first four questions with scores ranging from 0 and 4, with “Yes” having score = 1 and “No” = 0. Increased levels of adherence correspond with lower scores. Patient scores from 3 to 4 will be classified as low adherence, moderate adherence (score from 1 to 2), and high adherence (score = 0, with no answers with yes) [49] (Table 1).

Table 1: Medication adherence questionnaire scoring scheme

| Adherence questionnaire scores |
| --- |
| High adherence = 0 item answered “Yes” |
| Moderate adherence= 1 or 2 items answered “Yes” |
| Low adherence= 3 or 4 items answered “Yes” |

1. Medication Therapy Management (MTM) Program

As a new component of the MPIP, the MTM program will be made available to the clinic’s ambulatory service for the first time, and the intervention group will receive the following interventions as part of the program:

- 1. Medication counselling and reconciliation

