## 2.10 Statistical Analysis

The sample size required to reach significant in the three primary outcomes in the study’s multi-intervention approach is 180 participant (90 participants in each group). Sample size was calculated with Giga sample size online calculator [69], according to a pilot analysis of 50 participants matching study protocol, with a power of 80% with alpha level of 5% to detect the minimal difference of each primary outcomes in the study.

For 1^st^ outcome, the baseline medication possession ratio (MPR) for those 50 participants was 0.93 ± 0.09 (mean ± SD), we determined that a target of 82 participants per group would be required for a minimum detectable effect of 0.035 between both groups. A total sample size of 180 was calculated, assuming dropout rate of 10% in both groups.

For 2^nd^ outcome, the mean body mass index (BMI) (mean ± SD) of the 50 participants was 31.2 ± 6.4, and the total number of participants required to detect minimum detectable difference of 2.5 in BMI between groups was 180 participants, powered for 80% with α equal to 0.05, considering drop rate of 10% throughout the study period.

In addition, for 3^rd^ outcome to detect minimal difference of 0.5% in HbA1c between groups with mean HbA1c = 7.7 ± 1.3 (mean ± SD) at baseline (for the same 50 participants), a total sample size of 184 participants were calculated with 84 participants per group were required, considering 10% expected dropout rate during the follow-up period.

For data analysis, the difference between both groups will be tested for normality using the Shapiro–Wilk test. Data will be presented as percentages for categorical variables or mean ± SD or median (25th, 75th percentiles) for continuous variables. Chi-square test will be used for the categorical variables, whereas student’s t-test will be used for normally distributed continuous variables, or Mann–Whitney U test for non-normally distributed continuous variables.

Analyses will be performed using IBM SPSS Statistics (version 26), and differences will be considered significant for a p-value of <0.05.

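### The 0–4 adherence questionnaire is given three ordered classes, but the only test named for categorical data ignores order; the protocol should fix which form is compared and use a baseline-adjusted ordinal method

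*Protocol*

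**What the plan says.** Protocol section 1.3 lists as its first primary outcome "to evaluate the impact of pharmacist-led MTM on medications adherence" and names no instrument there. Section 1.4 supplies the instruments and the direction of the aim: "Improve medication adherence measured by fixed medication possession ratio (MPR) equation and a validated questionnaire". Section 2.8.1 repeats the pairing and says that adherence is evaluated by "calculating the medication adherence possession ratio and the medication adherence questionnaire scores".

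Under Medication Adherence Questionnaire, section 2.8.1 defines a four-item total with "scores ranging from 0 and 4, with “Yes” having score = 1 and “No” = 0", lower being better. It then sets the classes: "Patient scores from 3 to 4 will be classified as low adherence, moderate adherence (score from 1 to 2), and high adherence (score = 0". Table 1 repeats them. The questionnaire is given to all participants at baseline and again at exit.

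Section 2.10 gives general rules by type of variable. For categories: "Chi-square test will be used for the categorical variables". For continuous variables it names the t-test, or the "Mann–Whitney U test for non-normally distributed continuous variables". It names no trend test, ordinal model or baseline-adjusted comparison. The sample size for the first outcome uses MPR only.

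**The concern.** A 2 × 3 chi-square test asks whether the class percentages differ in any way. It spends two degrees of freedom and would give the same answer if the classes were shuffled. The aim in section 1.4 is directional: better adherence in the intervention arm. The test can therefore miss a steady improvement that an ordered test would detect. It can also be significant when patients leave the middle class in both directions, which is not better adherence.

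Grouping also removes the difference between one and two missed items, and between three and four.

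The baseline score is collected in everyone, yet none of the named tests uses it.

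At stake is efficiency and clear interpretation on one of two measures of a primary outcome. The validity of the test is not in question: chi-square on three classes holds its nominal level.

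**Working it through.** **1. The plan's own figure for this outcome.** Inputs from section 2.10: MPR SD 0.09, difference 0.035, power 80%, alpha 5%, 82 per group.

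n = 2 × (z_alpha + z_power)² × (0.09/0.035)²

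- One-sided 5%: 2 × (1.645 + 0.842)² × 6.61 = 81.8, so 82. This matches.
- Two-sided 5%: 2 × (1.960 + 0.842)² × 6.61 = 103.8, so 104.

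The 82 concerns MPR only and is used below simply as the group size. Its one-sided basis is a separate matter. The protocol gives no effect, distribution or power for the questionnaire, so everything below rests on assumptions.

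**2. One setting by hand.** Assume that control scores 0, 1, 2, 3, 4 have frequencies 40, 25, 18, 10, 7%. Assume also that the intervention doubles the odds of being at or below every cut (proportional odds, OR 2).

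| Cut | Control | Odds | Doubled | Intervention |
|---|---|---|---|---|
| ≤ 0 | 0.40 | 0.667 | 1.333 | 0.571 |
| ≤ 1 | 0.65 | 1.857 | 3.714 | 0.788 |
| ≤ 2 | 0.83 | 4.882 | 9.765 | 0.907 |
| ≤ 3 | 0.93 | 13.286 | 26.571 | 0.964 |

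High/moderate/low is then 40.0/43.0/17.0% against 57.1/33.6/9.3%. The chi-square noncentrality is 82 × Σ(p − q)²/(p + q) = 82 × (0.0303 + 0.0116 + 0.0226) = 5.29.

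- With 2 degrees of freedom (critical value 5.99), power is about 53%.
- If nearly all of that signal went into 1 degree of freedom, as an ordered test allows, power would be Φ(√5.29 − 1.96) = Φ(0.34), about 63%.

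The second degree of freedom alone therefore costs about 10 points here.

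**3. Simulation.** 82 per arm, two-sided 5%, OR 2, 40,000 trials per row. Tests: Pearson chi-square on three classes, Mann–Whitney on the same classes, and Mann–Whitney on 0–4. Type I error was about 5% for all three.

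| Controls scoring 0 | Chi-square, 3 classes | Mann–Whitney, 3 classes | Mann–Whitney, 0–4 | Total loss | From ignoring order | From collapsing |
|---|---|---|---|---|---|---|
| 20% | 53.5% | 64.1% | 69.3% | 15.8 | 10.6 | 5.2 |
| 30% | 54.3% | 64.9% | 68.3% | 14.0 | 10.6 | 3.4 |
| 40% | 53.2% | 63.8% | 66.0% | 12.8 | 10.6 | 2.2 |
| 50% | 49.8% | 60.4% | 61.5% | 11.7 | 10.6 | 1.1 |
| 65% | 40.4% | 50.8% | 51.3% | 10.9 | 10.4 | 0.5 |

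Varying the effect, with about 15–70% of controls scoring 0:

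- OR 1.7–2.5, 82 per arm: loss 7.7–15.5 points.
- OR 3, 82 per arm: loss 4.4–10.1 points.
- OR 3, 90 per arm: loss 3.2–8.7 points.

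Over all proportional-odds settings tried, the loss is roughly 3–17 points, of which about 0–6 come from collapsing. This is not a bound. If only about 10% of controls scored 0 and most scored 1 or 2, the loss would be larger and more of it would come from collapsing.

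**4. Where the shift is not uniform.** Same control distribution (40/25/18/10/7%), 82 per arm:

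| Intervention scores 0–4, % | Chi-square, 3 classes | Mann–Whitney, 0–4 |
|---|---|---|
| 60/10/10/12/8 | 84.4% | 39.1% |
| 55/15/10/12/8 | 59.3% | 24.9% |
| 40/42/18/0/0 | 99.9% | 34.6% |
| 40/33/22/3/2 | 64.5% | 14.4% |
| 58/17/11/8/6 | 55.4% | 52.6% |

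Chi-square wins in all five, by about 3 to 65 points.

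**5. Direction.** With the same controls, let 20% of patients leave the moderate class and split equally between high and low. Chi-square is significant in 71% of trials and Mann–Whitney in about 6–7%.

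**The case against.** The strongest reply is that no sentence assigns the questionnaire to chi-square. Section 2.8.1 speaks of scores and defines a 0–4 total. If that total fails the normality check in section 2.10, it goes to Mann–Whitney, which is one of the remedies proposed here. A reader might infer that the protocol commits this measure to an unordered test. The text does not support that. It leaves two tests open, and only the classified form meets the order-blind one.

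It can also be said that the choice between score and classes belongs in an analysis plan that is not shown. That would dispose of a bare omission. But section 2.10 does set a rule for categorical data and section 2.8.1 does create ordered categories, so what the protocol itself fixes fits the measure poorly. The classes follow a cited scoring scheme, and their use for description is not at fault.

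A reader might also infer a firm loss of 10–16 points, and a change with no downside. Neither holds. The loss depends on an assumed distribution, effect and uniform shift, and the sign reverses in the settings of step 4. Nor is the study left short of its stated power on this outcome, since that figure concerns MPR.

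Finally, the percentages called for in section 2.10 would show movement into both outer classes. That limits the risk of misreading but does not remove it.

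**Conclusion.** The point holds as a modest, conditional one. The protocol leaves open whether the 0–4 score or the three classes are compared. If the classes are, the only named test ignores order and direction. On either reading, no named test uses the baseline score.

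The cost, if the classes are tested, is roughly 3–17 points of power with about 82 per arm. This assumes a broadly uniform shift, two-sided 5%, and about 15–70% of controls scoring 0. Ignoring order accounts for most of it and collapsing for about 0–6 points. An ordinal method suits the directional aim in section 1.4, so the change is worth making.

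**What to change.** State in section 2.10 that the arms are compared on the exit 0–4 questionnaire score with an ordinal method. A proportional-odds model with the baseline score as covariate is preferable, because baseline is collected in all participants. Mann–Whitney, already named, is the simple alternative. Report the high, moderate and low classes as percentages by arm, for description only.

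The cost is one sentence and no new data. The small downside is lower power than chi-square if the effect is confined to one class boundary. The descriptive percentages would still show that pattern.

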# 1. Introduction

## 1.1 Background

The prevalence of type 2 diabetes mellitus (T2DM) is increasing worldwide, with the greatest increase occurring in low- and middle-income countries [1] . The prevalence of diabetes is the highest in the Middle East and North Africa, with approximately 10.9% of the adult population being diagnosed with T2DM [2]. The estimated number of deaths caused by diabetes and its complications reached 368,000 in 2013 in the Middle East and North Africa [3]. In particular, diabetic kidney disease (DKD) is the leading cause of end-stage kidney disease and substantially contributes to cardiovascular events [4].

New approaches of managing patients with diabetes, such as pharmacist-led medication therapy management (MTM) [5], the use of telemedicine technology through mobile applications [6], dietary and exercise interventions [7, 8], and intensive serum electrolyte panel monitoring [9] have been shown to be beneficial for monitoring and managing diabetes complications, including DKD progression. However, the impact of each intervention or a combination of such interventions has not been clearly elucidated.

Although there is evidence demonstrating the benefit of individual interventions for reducing the burden of chronic T2DM and DKD, the most effective multi-factorial intervention, particularly on UAE population, remains unclear. Such an intervention is likely to involve glycaemic control by promoting adherence to medication and lifestyle, such as diet and exercise and closely monitoring to blood electrolyte levels. These factors have a long-term effect on DKD progression and hard end points, such as cardiovascular events and all-cause mortality [10].

In this study, we will examine the effect of these interventions in a combined multifactorial approach called Pharmacy Intervention Protocol (MPIP), and we will use the Abu Dhabi Health Services Company (SEHA) mobile application, which enables the patient to have access to his medical record, medications, and to book future appointments. The impact and usefulness of the application will be examined in the new pharmacy intervention protocol. Other studies have investigated similar tools in the treatment of patients with complex diseases, who require more frequent visits to achieve tighter glycaemic control or face difficulties in accessing the healthcare system [11].

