Patients will be advised to bring the medication booklet to each follow-up visit to update the next refill schedule or any changes in their profiles. Moreover, it will be used as a reference during Salamtak downtime or when patients’ medical records from other private facilities are not available.

- 1. SEHA Mobile Application

Despite the fact that the SEHA mobile application [50] is accessible to all patients for download and usage, the patients often do not know how to use its features. As a new initiative in the MTM program, participants in the intervention group will receive face-to-face educational sessions for 5 minutes on the use of the SEHA mobile application, how to read the clinical information and laboratory results, extract their medication profile, add OTC medications to their medical record, and read notifications for medication approval from insurance as well as for subsequent medication refills.

The SEHA mobile application provides real-time individualised feedback, including patient access to Salamtak, laboratory test results, radiology reports, medications, allergies, immunisation records, and health maintenance history for patient visits occurring in SEHA facilities. Moreover, it enables patients to request or reschedule appointments or reschedule them, and search for a healthcare facility. The application sends a short message service (SMS) to the registered mobile number for appointments, with reminder notifications to remain keep the patient informed about future or follow-up appointments.

At the end of the study, we will use the SEHA mobile, and booklet use questionnaire to record the number of participants in each group using the application on their mobile device and the extent of application utilisation (Appendix 6). The results will be correlated with medication adherence to measure the effect of online technology on medication management.

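### Correlating app use with adherence, with no mention of arm, mixes any app effect with that of the whole intervention package and cannot be read as an effect of the technology

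*Protocol*

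**What the plan says.** Section 1.1 of the protocol announces an interest in the app: "The impact and usefulness of the application will be examined in the new pharmacy intervention protocol". The only analysis given for it is in section 2.8.1, in the part on the SEHA mobile application. A questionnaire at study end will "record the number of participants in each group using the application on their mobile device and the extent of application utilisation". Under the next sentence, the results will be "correlated with medication adherence to measure the effect of online technology" on medication management.

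The same part states that the app "is accessible to all patients for download and usage, the patients often do not know how to use its features". As the new initiative, "participants in the intervention group will receive face-to-face educational sessions for 5 minutes on the use of the SEHA mobile application". Controls can therefore use the app, but they are not taught to.

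The intervention arm also receives other adherence support that controls do not get. "Each participant in the intervention group will receive a 15- to 30-min counselling session at the initial visit and each scheduled follow-up visit", and after each visit "each participant in the intervention group will receive a 15-minute follow-up phone interview within two weeks for adherence reinforcement". Medication therapy management and the pocket medication booklet are likewise given to that arm only.

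Section 2.10 lists the chi-square, t and Mann-Whitney U tests. Neither that section nor section 2.8.1 says how arm enters the app correlation.

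**The concern.** Assignment to the intervention arm is meant to raise app use (through the training) and to raise adherence (through counselling, calls, medication therapy management and booklet). Arm is thus a common cause of the two variables being correlated. If the trial works as intended, a correlation over all patients will be positive even when the app contributes nothing, and the stated purpose would label that result an effect of online technology.

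There is a second problem that arm does not explain. Whether a patient uses the app is that patient's choice, and patients who take their medicines reliably may also be the ones who use it. That bias exists inside each arm.

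At stake is a misattribution: a clinic might credit the app with a gain that came from pharmacist time.

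**Working it through.** **Inputs from the protocol.** MPR mean 0.93, SD 0.09, detectable difference 0.035 and 82 per group (section 2.10); 1:1 allocation (Figure 1); MPR capped at 1 (section 2.8.1).

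**Assumptions.** The true app effect is zero. App use is yes/no, although its extent is also recorded. Adherence is MPR, since the sentence does not name the measure. The correlation is tested two-sided at 5%. The shares using the app in each arm are assumed.

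**The protocol's own figure.** The app correlation has no stated figure. The nearest is 82 per group for MPR: n = 2 × (1.645 + 0.842)² × (0.09/0.035)² = 2 × 6.18 × 6.61 ≈ 82. It reproduces with a one-sided 5% test and 80% power (two-sided gives 104). It is used here only as the number per arm.

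**Step 1: correlation of arm with MPR.** With equal arms, (0.035/2) / √(0.09² + 0.0175²) = 0.0175 / 0.0917 = 0.191.

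**Step 2: correlation of arm with app use.** With shares p_C (control) and p_I (intervention) and mean p, φ = [(p_I − p_C)/2] / √(p(1 − p)).

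**Step 3: correlation of app use with MPR.** With no app effect, the two are linked only through arm, so the expected pooled correlation is r = 0.191 × φ.

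**Step 4: chance of a significant result.** By the Fisher transformation with 164 patients, z = atanh(r) × √161. The rate is P(Z > 1.96 − z) + P(Z < −1.96 − z).

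| Assumed app use, control / intervention | φ | r | z | Falsely significant |
|---|---|---|---|---|
| 40% / 60% | 0.10/0.500 = 0.200 | 0.038 | 0.48 | 8% |
| 70% / 90% | 0.10/0.400 = 0.250 | 0.048 | 0.61 | 9% |
| 50% / 80% | 0.15/0.477 = 0.314 | 0.060 | 0.76 | 12% |
| 40% / 90% | 0.25/0.477 = 0.524 | 0.100 | 1.27 | 25% |
| 20% / 90% | 0.35/0.497 = 0.704 | 0.134 | 1.71 | 40% |

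Simulation of the same set-up agrees. With equal use in both arms (50%/50%), or with no arm difference in MPR, the rate stays near 5%.

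**Size on the MPR scale.** The spurious difference between users and non-users is 0.035 × [p_I/(p_I + p_C) − (1 − p_I)/(2 − p_I − p_C)]. At 40%/90% this is 0.035 × (0.692 − 0.143) = 0.019, more than half of the arm difference.

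**Effect of the cap.** Capping simulated MPR at 1 lowers the rates slightly: from 7.7% to 7.0% at 40%/60%, from 17% to 15% at 30%/70%, and from 32% to 29% at 30%/90%.

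**What adjusting for arm achieves.** With arm means removed and no self-selection, the simulated rate returns to about 5% (4.7% to 5.5%, uncapped MPR). If self-selection is added as an assumed latent correlation of 0.2 between adherence and app use within arms, still with no app effect, the arm-adjusted test is significant in roughly 37% to 52% of trials.

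**The case against.** **Pooling is not written.** A reader might infer that the protocol prescribes one correlation over both arms. It does not say so. Recording use by group and then correlating the results could also mean one correlation per group, and a statistical analysis plan, not shown here, may settle it. This stands as a limit: pooling is the natural reading but remains an inference. The purpose clause does not depend on it. That clause claims an effect from a self-selected exposure, which is unsupported under either reading.

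**The app is not a listed outcome.** A reader of section 1.1 might treat its evaluation as a formal objective. Sections 1.3 and 1.4 do not include it among the primary, secondary or expected outcomes, and no sample size rests on it. This stands and limits the weight of the point.

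**The gap in app use is unknown and may be small.** Section 2.5 excludes patients who cannot use mobile applications, and the app is open to everyone. At 70%/90% or 40%/60% the inflation is only to 8% or 9%. That is fair, and it is why a range is given. A reader might also suppose a larger arm difference and hence worse rates. Doubling it to 0.07 is not supported: 0.93 + 0.07 = 1.00 would put the intervention mean at the MPR cap.

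**Controls are not without support.** They receive baseline pharmacist counselling, counselling at the pharmacy counter and reminder calls. The arms differ in the repeated sessions, follow-up interviews, medication therapy management, booklet and app training. That is enough for arm to be a common cause.

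**Conclusion.** The point holds as a limited one. As naturally read, the stated analysis is confounded by arm. With no app effect it would be falsely significant in about 8% to 40% of trials rather than 5%, given the protocol's MPR difference, SD and number per arm. The direction of the bias needs only that app use and adherence are both higher in the intervention arm, as the package intends. Its size rests on the assumed app-use shares.

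It would be tempting to conclude that adding arm as a covariate rescues the claim of an effect. The documents do not support that: app use is not randomised within either arm, and modest self-selection keeps the error rate far above 5% after adjustment. Nor does the point touch the randomised comparisons, which do not use app use at all. The analysis is exploratory, and the correction is desirable rather than critical.

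**What to change.** In section 2.8.1, state that the relation between app use and adherence will be estimated within each arm, or in one model with arm and the baseline adherence questionnaire score as covariates. That score is already collected from all participants. Name the adherence measure to be used.

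Replace the purpose clause in "The results will be correlated with medication adherence to measure the effect of online technology on medication management" with wording that reports an exploratory association, and note that app use is self-selected. This rewording is needed whichever analysis is chosen, because adjustment for arm removes only the confounding by arm.

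The cost is one or two covariates and a sentence of text, with no new data. The downside is some loss of precision if nearly all intervention patients use the app, since few non-users would remain in that arm for comparison.
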